## Screening examination

During screening, the following will take place:

- Endorsement of informed consent
- Medical history, heredity, drug use, weight history
- Status (heart, lung, abdominal status, sitting blood pressure and heart rate), height, weight, waist circumference, hip measurements
- Routine blood test analysis (Sentto Kemlab): HbA1c, blood status, creatine, ALT, ALP, ferritin, glucose, hsCRP and TSH, Pt-eGFR (Cystatin C)
- Supplementing liver investigation if not previously performed (hepatitis serology, autoantibodies, protein fractions)

## Baseline samples

If a patient meets the inclusion criteria and has no post-screening exclusion criteria, the following baseline tests will be performed after a 8-hour overnight fast. (*Participants should not have fasted the day before taking blood tests.*) The examinations are done at the Hepatological Unit, Huddinge and the Radiology Clinic, Huddinge. A total of 120 ml of blood is taken at baseline.

- Triglycerides, total cholesterol, LDL cholesterol, HDL cholesterol, AST, ALT, ALP, GT, insulin, glucose, C-peptide, ApoB/ApoA1 ratio, TSH (sent to Kemlab)
- Urine test: ketones in urine (checked with urine strips at reception).
- Research blood samples (serum, heparin plasma and EDTA plasma), which are stored after centrifugation as noted below in cryotubes (0.5 ml/tube) and frozen for later analysis for the following parameters: markers of vascular inflammation and oxidative stress, GH, IGF-I, IGFBP-1, IGFBP-2, leptin, adiponectin, CK-18 fragments and fatty acid composition in plasma (e.g., for validation of the diet diary). The samples are saved as serum (7 x 0.5 ml), EDTA plasma (3 x 0.5 ml) and heparin plasma (4 x 0.5 ml) in cryotubes with 0.5 ml/tube at -70°C.

- Urine sample: 8 ml of morning urine is frozen at -70°C for later analyses of parameters reflecting oxidative stress and metabolomics.
- Feces test: The participant receives a stool test kit with sampling instructions at the screening visit. The sample will be included in the baseline examination. The sample is saved at -70°C for later analysis of the composition of microbiota and metabolites (see Appendix 2). The composition of the microbiota is analyzed using DNA technology (either that the 16SrRNA gene is amplified and sequenced or metagenomics in which the entire bacterial genome is sequenced).
- Whole blood for DNA analysis for the determination of polymorphisms related to NAFLD (PNPLA3, TM6SF2, et al.) (7 ml). Saved at -70°C.
- Elastography with FibroScan to measure liver stiffness and measurement of fat content with CAP.
- MRI scans of the liver to measure fat content (including body composition and fat distribution) will be performed at the MRI unit, Karolinska Huddinge. The measurement is done without a contrast agent and takes about 45 minutes. During the measurement, a short-term vibration wave is sent in from the right flank to measure liver stiffness. In one-third of the patients, methodological control of reproducibility will be carried out by conducting 2 MRI examinations at the same occasion.
- Bioimpedance measurement via the arms and legs (measurement of body composition, non-invasive and risk-free).
- Upper arm muscle circumference and triceps skin folds will be measured with a measuring tape and calipers.
- Oral glucose tolerance test – (OGTT).
- 3-day diet diary will be applied to compare the patient's food intake before the start of the study and after the intervention. The diet diary will be validated by blood tests to analyze fatty acid composition in plasma.

- Participants will be asked to complete validated internet-based questionnaires on physical activity level (Active-Q®), eating habits (Meal-Q®), alcohol habits (AUDIT), Consolation Eating Survey, Ladder of Life.

### **Randomization and dietary treatment**

- After baseline samples, patients will be randomized 1:1:1 to the LCHF, 5:2, or placebo diet (meaning standard lifestyle advice according to clinical practice, see Appendix 3). The study is planned to last for 3 years, so that every three to six months, 5-10 participants per group are randomized. Each group will be randomized to one of the respective diets. Group information will be given about diet at a meeting for each group, at which time menus will be distributed.
- **The 5:2 diet** for women means that for 2 days a week, they eat 25% (= 500 kcal of intake of 2000 kcal/day) and for the other 5 days of the week, eat the full 2000 kcal/day. Hence, a total of 11,000 kcal/week, which, on average, gives about 1,556 kcal/day. For men, 600 kcal/day are consumed during the fasting days, calculated on a 2,400-kcal daily intake, resulting in a weekly intake of 13,200 kcal = 1,886 kcal/day. For variation, each participant has energy-calculated menus to choose from for breakfast, lunch and dinner during the "fasting days".

Information about the Nordic nutritional recommendations will be given as an alternative on the 5 days when the participants eat freely. They can decide for themselves two or three meals per day, choosing from four alternatives for each meal. Participants may vary between the selected menus during the days of fasting. During the study, the participants will be instructed to record in a diary which menu they choose and which day of the week and whether they follow the menu or not. The diary will be distributed during the information meeting and the participants will take it with them at the return visit.

- **The LCHF diet** implies a restriction on carbohydrate intake to a maximum of 10% of the total energy intake. Approximate energy distribution will be about 5-10E% carbohydrates, 50-80 E% fat and 15-40 E% protein. The group is instructed to maintain a diet with approximately the same calorie intake as the 5: 2 distribution over the week, i.e. an average of about 1,600 kcal/day for women and 1,900 kcal/day for men. The diet is based on the intake of meat, fish, eggs, surface vegetables, vegetable oils and dairy fats (e.g., butter, cream, cheese). Minimized will be the intake of sugary drinks, juice, sugar, bread, pasta, rice, pie, potatoes and other carbohydrate-rich foods, including certain fruits.
- **The placebo diet** means that patients are informed about the diet by their doctor at the clinic in accordance with clinical practice. They are not informed about a specific diet, or group information or dietician contact. The dietary advice includes, among other things, a reduction in the intake of sweets, avoidance of excessive portions, eating three meals a day regularly and do not drink more than a maximum of 10 standard glasses of alcohol (one standard glass corresponds to 12-14 grams of pure alcohol) per week (see Appendix 3).

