### **Method**

Patients are recruited via three routes: (1) patients with known NAFLD who are followed at the liver clinic at the Gastro center; (2) patients referred to the Gastro center from primary care for investigation of suspected NAFLD; and (3) by an advertisement in the local press

(see Appendix 1). Patients are called to a doctor's appointment at the liver clinic where they are informed about the study orally and in writing.

Patients who meet the inclusion criteria and sign the informed consent form are screened for any exclusion criteria. After screening and inclusion, baseline tests are performed (specified below). A total of 75 patients, balanced for sex, will be randomized to either treatment with the LCHF diet, 5:2 diet, or placebo (see below). The diet intervention takes place in collaboration with [name]'s research group at Karolinska. Solna by dietitians and doctors. Methodology and infrastructure have been developed through other diet intervention studies, with logistics that have been tested on >100 patients with and without type2 diabetes. At both the start and conclusion of the study, the liver's fat content is checked with an MRI and liver stiffness with elastography. Differences in fat content and liver stiffness will be statistically analyzed using the rank-sum-test primarily according to the intention-to-treat principle as well as in sensitivity analysis by the per-protocol principle.

Because there are no data on the effect of diets on the reduction of liver fat, it is difficult to perform a power analysis. If data are extrapolated from other weight loss interventions where liver fat data are available and assume that dietary intervention groups will lose approximately 5% of their weight over three months, this represents approximately 30% reduction in liver fat. Assuming that the placebo group reduces the amount of fat in the liver by 10%, and with a standard deviation of 20%, at least 16 people in each arm will be needed to see differences between the groups with 80% power and an alpha value of 0.05. Because some loss of participants can be expected to occur, we want to include 25 people in each arm.

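### The protocol leaves unclear whether patients or groups are randomised, and its plain rank-sum test ignores both batch and teaching group; the effect is mild over-caution or excess false positives, depending on the unit

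*Protocol*

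**What the plan says.** Protocol, Randomization and dietary treatment: "patients will be randomized 1:1:1 to the LCHF, 5:2, or placebo diet", and over a planned 3 years "every three to six months, 5-10 participants per group are randomized". The sentence that follows states that it is each group that is randomised to a diet. The section then describes a diet meeting for each group.

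Protocol, Start of treatment: the 5:2 and LCHF patients are taught in groups of about 5-8, on separate occasions, according to their randomised diet. The description of the placebo diet says that control patients get advice from their doctor and no group session.

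Protocol, Method: "Differences in fat content and liver stiffness will be statistically analyzed using the rank-sum-test", by intention to treat first and per protocol as a sensitivity analysis. Neither batch nor group is mentioned. The sample size treats patients as independent: "at least 16 people in each arm will be needed", raised because of expected losses to the point where "we want to include 25 people in each arm".

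**The concern.** The named test compares every patient with every other patient, whatever the batch or teaching group. What this does depends on a fact on which the protocol gives two answers.

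- **Patients randomised within batches.** Season, staff or scanner differences between batches are balanced across arms by design, but the pooled test still counts them as noise. Its p-values are somewhat too large, and some power is given away.
- **Whole groups randomised.** Group differences fall together with diet and do not cancel. The p-values are too small.
- **Patients randomised, diet arms then taught in groups.** Any likeness created by shared sessions exists only in the diet arms and again does not cancel.

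The primary result could therefore be slightly too cautious or materially too optimistic, and the document does not let a reader tell which.

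**Working it through.** **1. The plan's own figure.** Inputs from Method: "this represents approximately 30% reduction in liver fat" in the diet arms; "the placebo group reduces the amount of fat in the liver by 10%, and with a standard deviation of 20" per cent; "with 80% power and an alpha value of 0.05". Sidedness is not stated; two-sided is assumed.

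n per arm = 2 × (1.96 + 0.84)² × 20² / (30 − 10)² = 15.7, so 16. This matches the protocol. The formula assumes independent patients. The planned 25 tolerates 1 − 16/25 = 36% loss.

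**2. Patients as the unit, batch effects shared by all arms.** The documents give no batch variance, so its share of the total is assumed at 0-20%. Simulation of two arms: normal change, total SD 20, difference 20, two-sided 5%, 40,000 trials per setting. There are 5 batches of 5 per arm (25) or 4 batches of 4 (16). The aligned test subtracts the batch mean before ranking and takes its variance from permutation within batch.

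| Batch share | Pooled type I error | Power at 25: pooled / aligned | Power at 16: pooled / aligned |
|---|---|---|---|
| 0% | 5.1% | 91.8 / 92.0 | 75.1 / 75.7 |
| 5% | 4.4% | 92.7 / 93.4 | 75.9 / 78.0 |
| 10% | 4.1% | 93.3 / 94.6 | 76.8 / 80.2 |
| 20% | 3.4% | 94.3 / 96.4 | 78.2 / 84.4 |

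The aligned test holds about 5% throughout. The gain in power is 0.2, 0.7, 1.3 and 2.1 points at 25 per arm, and 0.6, 2.1, 3.4 and 6.2 points at 16. A separate run of 12,000 trials gave pooled type I error of 4.9% down to 3.2%, and similar power. A linear model with batch as a fixed factor reached 93.1 / 94.4 / 95.5 / 97.0% at 25 and 77.9 / 80.0 / 82.2 / 86.3% at 16. Part of that gain comes from leaving ranks under a normal outcome, since it is already 77.9 − 75.1 = 2.8 points at share 0 with 16 per arm.

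**3. Whole groups as the unit.** The intraclass correlation (ICC) is not in the documents either; it is assumed at 0.05 / 0.10 / 0.20. Pooled type I error over 20,000 trials:

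- 5 groups of 5 per arm: 6.5 / 9.1 / 13.8%.
- 3 groups of 8 per arm: 8.7 / 12.8 / 20.5%.

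Batch alignment does not help. With 5 groups of 5 per arm and a 10% shared batch share added, pooled is 6.3 / 9.0 / 13.4% and aligned 7.7 / 11.0 / 17.3%. Removing the shared variance exposes the group variance.

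Sample size with design effect 1 + (m − 1) × ICC applied to 15.7:

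- m = 5: 15.7 × 1.20 = 19, × 1.40 = 22, × 1.80 = 29 per arm.
- m = 8: 15.7 × 1.35 = 22, × 1.70 = 27, × 2.40 = 38 per arm.

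These are rounded up and come before any allowance for losses.

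**4. Patients as the unit, likeness within diet teaching groups only.** With a 5% shared batch share and a diet-arm group effect of 5 / 10 / 20% (assumed), pooled type I error is 5.5 / 6.9 / 9.2% and aligned 6.1 / 7.9 / 10.6%.

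**5. Number of batches.** From the sample size, 25/10 to 25/5 gives 3-5 batches. From the schedule, 36 months at intervals of 6 to 3 months gives 6-12 occasions, hence 6 × 5 = 30 to 12 × 10 = 120 patients per arm. The two agree only if enrolment fills well under the full 3 years.

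**The case against.** The strongest reply is that this is minor and belongs in a statistical analysis plan, which is not shown. Handling of batches is often specified there, and the protocol does not say that batches will be ignored. At the planned 25 per arm the gain is at most about 2 points, and pooled power never falls below 91.8% against a target of 80%. The 6-point figure needs both 36% loss and an assumed 20% batch share. The usual stratified rank test (van Elteren) would do worse than the plan if batches do not differ: 89.4% against 91.8% at 25 per arm. All of this stands, and it keeps the priority down. It does not remove the contradiction on the unit of randomisation, which is in the protocol itself.

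Two stronger readings are tempting, and neither is supported. A reader might infer that the rank-sum test is simply conservative, so that a significant result is safe. That needs patients as the unit and no effect of shared teaching; the sentence on groups being randomised and the group sessions in the diet arms leave both open. A reader might equally infer that this is a cluster-randomised trial with badly inflated error. The Method section and the opening of the randomisation section speak of patients being randomised, and Start of treatment has teaching groups follow from the allocation. The sentence on groups may be loose wording.

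**Conclusion.** The concern holds in conditional form. The protocol contradicts itself on what is randomised, and the named test takes account of neither batch nor group. Individual randomisation is the better supported reading. On that reading, with batch effects shared by all arms, type I error is about 4.9% to 3.2%, and the power forgone is about 0-2 points at 25 per arm and 1-6 at 16. If groups are the unit, or teaching groups make outcomes alike, error exceeds 5%: about 6-14% with randomised groups of 5, and about 5.5-9% with clustering in the diet arms only. Every batch share and ICC here is an assumption, as are the normal outcome and the equal batches. Low to moderate priority: the reconciliation is necessary, while the batch adjustment is a cheap improvement.

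**What to change.** 1. In Randomization and dietary treatment, reconcile the two sentences so that one unit of randomisation is stated.
2. If it is the patient, amend Method to analyse the primary outcome by randomisation batch. Use either batch-aligned ranks with arm labels permuted within batch, or batch as a fixed factor in a model for the change in liver fat. Record batch and teaching group for every patient. Add a sensitivity analysis that allows for clustering by teaching group in the diet arms.
3. If it is the group, use an analysis that treats the group as the unit, and recheck the sample size, which assumes independent patients.
4. Take the number of batches from the actual enrolment schedule, and reconcile that schedule with 25 per arm.

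For the patient-level case the cost is a few sentences, two recorded variables and one degree of freedom fewer than the number of batches (2-4 for 3-5 batches), with no extra patients or procedures. If groups are the unit the cost is larger: 3-5 groups per arm leave few independent units, and more patients may be needed.

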### **Start of treatment**

Treatment takes place separately for the 5:2 and LCHF groups in connection with visits to the endocrine clinic, Solna. The placebo group receives no intervention.

- Participants are given group information about diet and menu suggestions led by a dietitian and doctor at the endocrine unit in Solna. At the meeting, participants are informed in groups about the 5:2 method and the LCHF diet, depending on randomization (different groups at different times): Approximately 5-8 participants per group per occasion.

### **Phone follow-up with a dietician (5:2 and LCHF)**

Follow-up occurs after 2, 4 and 8 weeks of treatment. The dietician encourages continued dietary treatment and records adherence to diet.

### **Examinations after 6 weeks**

After 6 weeks, the patients will be called to a dietician and research nurse to undergo the following examinations:

- Weight control, abdominal range, hip circumference
- The participants will be asked to leave their dietary diaries (filled in for 3 days during the week before the 6-week control)
- Bioimpedance measurement
- Upper arm muscle circumference and triceps skinfolds measured with a measuring tape and calipers
- Complementary dietary information and menu suggestions
- Survey on physical activity level, alcohol habits (AUDIT), Comfort Eater survey, Ladder of Life, as well as questions about difficulties in adhering to the diet.
- Blood tests (liver status, blood lipids) and samples for fatty acid composition in plasma (e.g., to validate the dietary diary). In addition, serum and plasma samples for research will be taken in the same way as at baseline. In total, 90 ml of blood will be taken at the 6-week control.

### **Investigations at the end of the intervention (at 3 months)**

After 3 months, the following examinations are repeated after 8 hours of fasting.

*(Participants should not have fasted the day before taking blood.)* A total of 110ml of blood will be taken at the end of the study.

- HbA1c, blood status, creatine, ASAT, ALAT, ALP, GT, ferritin, glucose, triglycerides, total cholesterol, LDL cholesterol, HDL cholesterol, insulin, glucose, C-peptide, ApoB/ApoA1 ratio, hsCRP, HbA1c (sent to Kemlab)
- Urine test: ketones in urine (checked with urine strips at reception)
- Research blood samples (serum, heparin plasma and EDTA plasma), which are stored after centrifugation as noted below in cryotubes (0.5 ml/tubes), are taken for analysis of the following parameters: markers of vascular inflammation and oxidative stress for GH (growth hormone), IGF-I, IGFBP-1, IGFBP-2, leptin, adiponectin, cortisol, prolactin, sex hormones (free testosterone and free estradiol), apoptosis (CK-18 fragments) and samples for fatty acid composition in plasma (validation of the dietary diary). The samples will be saved as serum (7 x 0.5 ml), EDTA plasma (3 x 0.5 ml) and heparin plasma (4 x 0.5 ml) in cryotubes with 0.5 ml/tube at -70°C until later analyses.
- Urine tests: morning urine, 8 ml will be saved at -70°C for later analyses of parameters reflecting oxidative stress and metabolomics.
- Feces test: The participants will receive a stool test kit with sampling instructions at the screening visit. The samples will be taken at the examination. The sample will be saved at -70°C for later analysis of the composition of microbiota and metabolites.
- Elastography with FibroScan to measure liver stiffness, as well as measurement of fat content CAP.
- MRI scan with H1-MRS to measure total fat content in the liver will be performed at the MRI unit, Karolinska, Huddinge
- Weight control, abdominal range, hip circumference
- Upper arm muscle circumference and triceps skin folds will be measured with a measuring tape and calipers
- The participants will be asked to leave their dietary diaries (filled in for 3 days during the week before the 6-week control)

- The participants will be asked to leave their dietary diaries (filled in for 3 days in the week before the 3-month control, including registration of selected menus during the "fasting days")
- Bioimpedance measurement
- OGTT
- Survey on physical activity level (Active-Q®), eating habits (Meal-Q®), alcohol habits (AUDIT), Consolation Eater survey, Ladder of Life and difficulties in following the diet.

### **Follow-up**

To study the long-term effects of the treatment, patients will be asked to take part in further follow-ups after 6 and 12 months for bioimpedance, weight, waist circumference, blood tests (same as in the 3-month follow-up) and questionnaires, as well as an MRI scan after 12 months.

### **Patient benefits**

Fatty liver disease is the most common liver disease in the world, and a subgroup of these patients is at risk of developing severe complications. Being able to advise these patients on which diet is most effective in reducing the amount of fat in the liver can eventually affect liver-related morbidity and ultimately contribute to a reduction in overall mortality in this patient group. It can also contribute to a better quality of life if a more structured and equality-based treatment can be offered to patients.

### **Risks**

There is a potential risk that the LCHF diet may lead to an increase in fat retention in the liver. However, given the concomitant calorie restriction, the risk is considered minimal. At the 6-week control, fat retention will be evaluated through blood tests (control of triglycerides

and liver enzymes). If ALAT, ASAT, ALP, or bilirubin rises >3 times baseline levels, diet treatment will be discontinued.

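### The stopping rule compares bilirubin with baseline, but no listed screening or baseline test gives a bilirubin value

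*Protocol*

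**What the plan says.** The only laboratory stopping rule in the protocol stands under Risks: "If ALAT, ASAT, ALP, or bilirubin rises >3 times baseline levels, diet treatment will be discontinued". It follows the statement that the LCHF diet might increase liver fat, and that this will be looked at in the 6-week bloods through triglycerides and liver enzymes.

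The blood tests before treatment are itemised:

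- Screening examination, routine panel: "Routine blood test analysis (Sentto Kemlab): HbA1c, blood status, creatine, ALT, ALP, ferritin, glucose, hsCRP and TSH, Pt-eGFR (Cystatin C".
- Screening examination, conditional work-up: "Supplementing liver investigation if not previously performed (hepatitis serology, autoantibodies, protein fractions".
- Baseline samples, clinical chemistry: "Triglycerides, total cholesterol, LDL cholesterol, HDL cholesterol, AST, ALT, ALP, GT, insulin, glucose, C-peptide, ApoB/ApoA1 ratio, TSH (sent to Kemlab".
- Baseline samples, frozen for later analysis: "markers of vascular inflammation and oxidative stress, GH, IGF-I, IGFBP-1, IGFBP-2, leptin, adiponectin, CK-18 fragments and fatty acid composition in plasma".

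The section on examinations after 6 weeks is less specific: "Blood tests (liver status, blood lipids) and samples for fatty acid composition in plasma". It does not say which analytes make up the liver panel.

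**The concern.** A rule that triggers on a multiple of the patient's own baseline needs two values per marker: one before the diet and one on it. For bilirubin, no listed test supplies the first. Whoever reviews the 6-week results would then have to ignore that limb, take a value from outside the protocol, or substitute some other reference, and different staff could choose differently.

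What is at stake is whether a participant-protection rule can be carried out, and carried out uniformly, as written. A baseline that was not measured before the diet starts cannot be drawn afterwards. The frozen baseline samples are set aside for other named parameters, and nothing in the protocol provides for a bilirubin result from them in time for a decision at 6 weeks.

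**Working it through.** The protocol gives no figure to reproduce here. The check sets the four markers in the rule against each list that could supply a value for it. ALAT and ALT are the same enzyme under two abbreviations, as are ASAT and AST.

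| Marker in the rule | Screening examination | Baseline samples | 6 weeks |
|---|---|---|---|
| ALAT (ALT) | listed | listed | not itemised |
| ASAT (AST) | not listed | listed | not itemised |
| ALP | listed | listed | not itemised |
| Bilirubin | not listed | not listed | not itemised |

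1. *Baseline reference.* ALAT, ASAT and ALP each appear on the baseline list, so three of the four limbs have a denominator. ASAT is missing at screening, but this does no harm because it is measured at baseline. Bilirubin is on neither list.

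2. *Other possible sources before treatment.* The conditional liver work-up at screening is spelled out in its bracket, and bilirubin is not in it. The parameters named for the stored baseline serum and plasma do not include it. The word occurs nowhere in the protocol except in the Risks rule.

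3. *On-treatment value.* The 6-week visit is the only scheduled blood test between baseline and the end of the intervention; the dietician contacts at 2, 4 and 8 weeks are by telephone. Its liver panel may well include bilirubin. That would give the numerator of the comparison but not the denominator.

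4. *Who is affected.* The rule discontinues a diet treatment. The section on the start of treatment says that the placebo group receives no intervention, so the rule has something to stop only in the 5:2 and LCHF arms. With 25 planned per arm, that is 2 × 25 = 50 of 3 × 25 = 75 patients.

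**The case against.** The case for leaving this alone has several parts.

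*The rule still works.* The triggers are joined by an or, so losing one does not disable the others. The declared purpose of the 6-week check is to look at triglycerides and liver enzymes. Triglycerides, AST, ALT and ALP are all on the baseline list, and liver tests and lipids are drawn at 6 weeks. This stands. A reader might infer that the stopping rule as a whole is inoperable, or that patients would go unmonitored. The documents do not support either: the gap is confined to the bilirubin limb.

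*The lists may simply be incomplete.* They look loosely drafted; the 3-month list names HbA1c and glucose twice. A site might measure bilirubin as part of a usual liver panel. This is plausible, and it means one cannot say that no bilirubin value will exist in practice. It does not remove the mismatch. The screening and baseline lists name single analytes, down to GT and an apolipoprotein ratio, so an unlisted test cannot be taken as planned.

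Three further inferences are tempting and do not hold:

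- *That all 75 patients are affected.* A baseline bilirubin is unlisted for all of them, but only the two diet arms have a treatment to discontinue.
- *That entry with raised transaminases makes the gap worse.* The inclusion criteria do admit such patients, but the transaminases have their baseline. The argument says nothing about bilirubin.
- *That the absence of bilirubin from the 3-month list is part of the defect.* That visit falls at the end of the intervention, when no protocol diet remains to be stopped. The check that the rule accompanies is the one at 6 weeks.

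**Conclusion.** The point holds in a limited form. The Risks section and the laboratory lists disagree: the rule compares four markers with baseline, and the listed tests provide a baseline for three. Followed exactly as written, the bilirubin limb has no reference value in the two diet arms, about 50 patients, while the ALAT, ASAT and ALP limbs remain operable.

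This is an internal inconsistency in a safety provision, not a detail that could properly wait for a statistical analysis plan, since stopping rules and blood panels are protocol content. It does not touch randomisation, sample size, the primary outcome or its analysis. It deserves correction because it sits in the protocol's only stated stopping rule and is cheap to put right.

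The conclusion rests on two assumptions: that the itemised lists are complete as printed, and that recruitment reaches the planned 25 per arm. Confidence is high that the sections do not match. It is lower that bilirubin would in fact be missing, because a site could obtain it outside the listed panels.

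**What to change.** Reconcile the rule under Risks with the lists under Screening examination, Baseline samples and Examinations after 6 weeks, so that every marker the rule names is measured at baseline and again at 6 weeks. Itemise the 6-week liver panel as part of this, so that the on-treatment side of each comparison is also explicit.

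The sponsor decides which markers the rule uses, and the lists must then match it. No change to the 3-month list is needed for this purpose.

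The cost is small. The protocol already takes 120 ml of blood at baseline and 90 ml at 6 weeks, so the change is either one routine assay on blood already drawn or a change of wording, made in a minor amendment. It should be made before further participants start a diet, since a missing pre-treatment value cannot be collected later.
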